## Abstract

**Background:**

Sexual problems are frequently reported after treatment with radiotherapy (RT) for gynaecological cancer (GC), in particular after combined external beam radiotherapy and brachytherapy (EBRT+BT). Studies demonstrate that psychosexual support should include cognitive behavioural interventions and involvement of the patient’s partner, if available. Therefore, we developed a nurse-led sexual rehabilitation intervention, including these key components. The intervention was previously pilot-tested and results demonstrated that this intervention improves women’s sexual functioning and increases dilator compliance. The objective of the current study is to investigate the (cost-)effectiveness of the intervention compared to optimal care as usual (CAU). We expect that women who receive the intervention will report a statistically significant greater improvement in sexual functioning and – for women who receive EBRT+BT – higher compliance with dilator use, from baseline to 12 months post-RT than women who receive optimal care as usual (CAU).

**Methods/design:**

The intervention is evaluated in the SPARC (Sexual rehabilitation Programme After Radiotherapy for gynaecological Cancer) study, a multicentre, randomized controlled trial (RCT). The primary endpoint is sexual functioning. Secondary outcomes include body image, fear of sexual activity, sexual-, treatment-related- and psychological distress, health-related quality of life and relationship satisfaction. A cost-effectiveness analysis (CEA) will be conducted in which the costs of the intervention will be related to shifts in other health care costs and the impact on patient outcome. The study sample will consist of 220 women with GC treated with RT in specialized GC treatment centres (N = 10). Participants are randomized to either the intervention- or CAU control group (1:1), and within each centre stratified by type of radiotherapy (EBRT+BT vs. EBRT only) and having a partner (yes/no). All women complete questionnaires at baseline (T1) and at 1, 3, 6, and 12 months post-RT (T2, T3, T4 and T5, respectively).

**Discussion:**

There is a need to improve sexual functioning after RT for GC. This RCT will provide evidence about the (cost-)effectiveness of a nurse-led sexual rehabilitation intervention. If proven effective, the intervention will be a much needed addition to care offered to GC survivors and will result in improved quality of life.

**Trial registration:**

ClinicalTrials.gov, NCT03611517. Registered 2 August 2018.

## Background

In the Netherlands, more than 4500 women are diagnosed with gynaecological cancers (GC) annually [1]. Approximately one-third of GC patients, especially those with cervical, uterine and vaginal cancers, receive radiotherapy (RT) as primary or post-surgical treatment; most often external beam radiotherapy (EBRT) with or without brachytherapy (BT). Sexual problems, such as dyspareunia, vaginal dryness and a decrease of sexual satisfaction and desire are frequently reported after treatment with RT for GC [2–9]. The negative effects of RT, and in particular of the combination of EBRT with BT (EBRT+BT), on sexual functioning are due to vaginal changes such as fibrosis with vaginal shortening and tightening, mucosal atrophy, and reduced flexibility and decreased lubrication of the upper vagina [10]. EBRT+BT is the standard combination for primary treatment of more advanced stages of cervical, vaginal and endometrial cancer, while postoperative BT is only added in case of involved or tight vaginal margins.

To prevent or reduce vaginal shortening and tightening during the period of fibrosis formation after EBRT+BT, it is generally recommended to use vaginal dilators for a period of 9-12 months after completion of treatment [11]. Such use may prevent or minimise vaginal stenosis with the purpose to maintain the option of vaginal penetration in the long term [11, 12]. Despite the proposed benefits of regular dilator use, most GC patients (75%) fail to use dilators regularly even after counselling and instructions for use [13–16]. Frequently reported barriers to dilator use are difficulties with planning, lack of time or privacy, forgetting, and other problems in the recovery phase such as fatigue and worry [17]. To increase compliance, it is important to provide sufficient patient information tailored to the woman’s need, clear instructions and psycho-education regarding dilator use [18]. In addition, the process of recovery from cancer diagnosis and treatment and the associated physical and psychological problems is already demanding. A broader view on rehabilitation, counselling and support would be needed to help multi-dimensional recovery and increase compliance with regular dilator use.

A recent study demonstrated that GC patients treated with RT benefit from a psychosexual rehabilitation information booklet [19]. Women reported more knowledge regarding physical and psychosexual side-effects and rehabilitation options in the first 6 months post-RT than women wo received standard information materials. However, the psychosexual rehabilitation booklet did not increase compliance with dilator use. In addition to psycho-education, two studies demonstrated that a psychoeducational group intervention, including a focus on motivation to engage in regular dilator use, increased dilator compliance [15, 20]. Indicating that GC survivors could benefit from additional professional support targeting dilator use. However, such an intervention targeting dilator use only did not affect the psychosexual consequences of treatment of GC, such as decreased sexual desire, dyspareunia, diminished body image, and relationship dissatisfaction [15]. Therefore, psychosexual rehabilitation interventions should focus on preventing and reducing RT-induced vaginal changes, as well as on increasing psychosexual and relationship satisfaction [21].

Only few studies have evaluated psychosexual rehabilitation interventions – which used cognitive behavioural techniques, psycho-education and counselling – for GC survivors [22–26]. Results demonstrated that women who received the psychosexual rehabilitation interventions experienced better sexual functioning, less sexual distress [23] and a decrease in sexual problems [22]. Only one of the studies actively involved the partner in the intervention and demonstrated that a couple-coping training improved sexual relationship satisfaction to a greater extent than medical information education or patient-coping training only [26].

It can be concluded that psychosexual support after treatment for GC should include motivational issues and psychosexual interventions to increase dilator compliance and improve sexual functioning. Furthermore, involvement of the partner is preferred. There is a need for a condensed, practical and (cost-)effective sexual rehabilitation intervention, consisting of psycho-education combined with elements of psychosexual-based cognitive behavioural therapy for GC patients and their partners after RT [27–31]. Therefore, based on the results of our previous studies [17, 18, 21], we developed a nurse-led sexual rehabilitation intervention to support sexual improvement and vaginal dilator use after RT. The intervention has multiple aims: motivating women, giving tailored advice, strengthening self-management, promoting couples’ mutual coping and support processes and, for women who received EBRT+BT, providing information and coaching on use of vaginal dilators on a regular basis. The results of our pilot study regarding the feasibility of the intervention demonstrated that this intervention improved women’s sexual functioning and that it supported them in their dilator use [32]. Furthermore, the nurses who were trained and supervised to guide the intervention felt capable to support the women.

In this manuscript we present the design of the SPARC (Sexual rehabilitation Programme After Radiotherapy for gynaecological Cancer) study, a multicentre randomized controlled trial (RCT) which evaluates the (cost-)effectiveness of the nurse-led sexual rehabilitation intervention in improving sexual functioning and dilator use of GC patients after RT. Participants are randomized to either the intervention- or optimal care as usual (CAU) control group (1:1). We expect that women who receive the intervention will report a statistically significant greater improvement in sexual functioning and – for women who receive EBRT+BT – higher compliance with dilator use, from baseline to 12 months post-RT than women who receive CAU.

## Methods

The study design and main procedures of the RCT are displayed in Fig. 1.

**Fig. 1 Fig1:**
[figure not shown]
Overview of study procedures. *The physical examination at the 6 months follow-up visit might also be conducted by the gynaecologist (depending on the centre). BT = Brachytherapy; EBRT = External Beam Radiotherapy; GC = Gynaecological cancer; RT = Radiotherapy; T1 = Self-report baseline questionnaire, T2-5 = Self-report follow-up questionnaires

### Ethical issues, safety aspects and (medical) complications

The SPARC study has been approved by the Medical Ethical Committee Leiden-Den Haag-Delft (number NL62767.058.17) and by the institutional review boards of the 10 participating GC centres (the participating GC centres are included in the Acknowledgements section). Recruitment and data collection started in August, 2018 and is still ongoing at the date of publication of this manuscript. This study is monitored on data and safety by an independent certificated study monitor. All study-related adverse events, i.e. dilator-use-related, will be recorded an reported as an adverse event. Events related to the undergone cancer treatments are not considered study-related events.

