### Recruitment and randomization

The treating radiation oncologists screen potential participants with regard to the inclusion and exclusion criteria. Eligible women are informed about the background, rationale and specifics of the study protocol. Women who want to participate in the study provide written informed consent and complete a paper-and-pencil baseline questionnaire before randomization. After inclusion, participants are assigned a unique study identifier by the local data manager, which will be filled out on all questionnaires and used in the data files. Inclusion and randomization take place before the completion of RT. Participants are randomized to either the intervention- or the optimal CAU control group (1:1), and within each centre stratified by type of radiotherapy (EBRT+BT versus EBRT only) and having a partner (yes/no). The randomization is block stratified with varying block sizes, and is performed by the local data manager, using a secured web-based data-management system.

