### Study groups

One month after completion of RT, women in both study groups receive an information booklet. The information booklets, which contain specific information to improve knowledge and coping strategies regarding sexual rehabilitation after either EBRT+BT or EBRT only, are based on the booklet developed in the pilot study [32]. The booklets are provided in both a printed and online version. Women in both study groups who received EBRT+BT are given a dilator set and are advised to start vaginal dilation for 1 to 3 min, 2 to 3 times a week around 4 weeks after RT when the vagina is sufficiently healed [11, 18].

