#### Intervention group: the nurse-led sexual rehabilitation intervention

The intervention consists of four one-hour face-to-face sessions at 1, 3, 6, and 12 months post-RT. These sessions are planned synchronously with women’s radiation oncologist follow-up visits. An additional session is scheduled for women who received EBRT+BT at 2 months, during which potential barriers and problems with dilator use are discussed. Furthermore, if preferred, an extra follow-up session/telephone consultation of 30 min can be scheduled between 6 and 12 months after RT. If a woman is in a relationship, the partner is invited to accompany her in the sessions.

The sexual rehabilitation intervention consists of 11 modules. A description of the content of the modules is provided in Table 1. The modules include topics such as education regarding the specific cancer diagnosis and treatment, education on the importance of regular use of vaginal dilators (if applicable), discussing potential experienced barriers to dilator use (if applicable) and lubricant use, fear of penetration with dilators (if applicable) and fear of resuming sexual activity after cancer, promoting couples’ mutual coping and support processes and addressing sexual and body image concerns. The content of the intervention is a personalized programme tailored to the participant-specific psychological, relational and somatic factors. During a session, the oncology nurse selects the specific module(s) that fits the woman’s (and her partner’s) needs. The decision tree for module selection is provided in Fig. 2.

**Table 1 Tab1:** Description of the sexual rehabilitation intervention modules

**Module 1: Brief sexual history**	This module describes how the nurse can question the patient in-depth about sexual problems on various domains of sexual functioning, including sexual interest/arousal, orgasm, pain and sexual satisfaction. It also covers psycho-education about sexuality and the sexual response curve [33] and provides information about frequently occurring sexual problems and solutions.
**Module 2: Pain during intercourse**	This module includes practical guidelines that the nurse can provide regarding pain during intercourse after radiotherapy-, with referrals to module 3, 4, 6 and 7, and explains how to provide psycho-education about the circular model of dyspareunia [34], which is based on a cognitive behavioural framework.

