**Module 3: Vaginal dryness and health**	This module provides the nurse with instructions on how to give advice with regard to treatment of vaginal dryness, pain or irritation. It also includes information regarding vaginal health, such as the use of vaginal creams, avoidance of scratching in response to irritated skin or avoidance of washing with soap.
**Module 4: Alternatives for intercourse**	The exercise in this module helps the woman and her partner (if available) to explore and discuss non-penetrative alternatives for sexual intercourse.
**Module 5: The partner and possible sexual problems**	This module can be consulted by the nurse when partners experience temporary sexual problems, such as erectile dysfunction during intercourse. The module also includes a reference to module 1.
**Module 6: Gradual exposure towards sexual intercourse**	The aim of the steps in this module, which are based on a cognitive behavioural gradual exposure therapy for Genito-Pelvic/Penetration Disorder [29], is to learn the woman and her partner how to re-engage in sexual intercourse. The steps include: touching of the vaginal opening with the erect penis without penetration, stepwise vaginal insertion of the erect penis without moving, and vaginal insertion of the erect penis with moving.
**Module 7: Pelvic floor exercise**	This module includes several pelvic floor relaxation exercises for women who experience tension in the pelvic floor muscles.
**Module 8: Difficulties with dilator use at home**	This module is suitable for women who experience problems with dilator use and who already practiced under supervision of a nurse (see module 9) or for women who do not want to practice under supervision. This module provides the nurse with instructions on how to give specific advice on how to overcome experienced difficulties, after first exploring the problems during dilator use (e.g. pain/discharge, loss of blood or difficulties with inserting the dilator).

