**Module 9: Using dilators under supervision at the outpatient clinic**	This module focuses on women who experience fear with regard to dilator use or who experience difficulties when using vaginal dilators, due to for example tension of the pelvic floor. The nurse-led session is based on therapist-aided exposure therapy for Genito-Pelvic/Penetration Disorder [29]. The goal is to reduce fear of dilator use by using a stepwise exposure session in which the woman - who performs the vaginal dilation by herself - is facilitated by the nurse. During the session, tips are given with regard to a correct and more comfortable use of the dilators. Furthermore, the nurse helps to evaluate and articulate any unhelpful cognitions about what could (or could not) occur during dilator use. In these instances, the exposure is used as a behavioural experiment, to test the tenability of these cognitions. The module also includes advice on how to handle problems that might occur during practicing at home.
**Module 10: Exploring and resolving ambivalence with regard to dilator use**	The aim of the exercise in this module is to motivate the woman for dilator use, by acknowledging, exploring and resolving ambivalent feelings towards dilator use by motivational interviewing technique [35]. By exploring pros and cons of both dilator use and no dilator use, the woman can be supported in making an informed choice about dilator use. If she decides to use dilators, problems with dilator use are discussed in more detail and how to overcome them. If a woman decides not to use dilators, tampons covered in petroleum jelly (Vaseline) are recommended and guidelines on how to use these are provided to the woman (see module 11).
**Module 11: Petroleum jelly (Vaseline) tampons**	This module follows module 10, when a woman decides not to use dilators. The module covers guidelines on how to use tampons covered in petroleum jelly (Vaseline).

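### The adverse-event rule covers only dilator-related events, so event-level harms of the non-dilator components, and any event in EBRT-only women, fall outside it

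*Protocol article*

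**What the plan says.** The safety section of the protocol article (Ethical issues, safety aspects and (medical) complications) gives the recording rule in two sentences. The first is "All study-related adverse events, i.e. dilator-use-related, will be recorded an reported as an adverse event". The second narrows it from the other side: "Events related to the undergone cancer treatments are not considered study-related events".

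Under Study groups, the article states who gets dilators: "Women in both study groups who received EBRT+BT are given a dilator set". The control-group section offers the set only where it applies. Women treated with EBRT alone are eligible (Study Sample) and form a randomization stratum (Recruitment and randomization).

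The intervention section states: "The sexual rehabilitation intervention consists of 11 modules". Table 1 describes them. The aim of module 6 "is to learn the woman and her partner how to re-engage in sexual intercourse", and its steps include "stepwise vaginal insertion of the erect penis without moving, and vaginal insertion of the erect penis with moving". Module 7 contains pelvic floor relaxation exercises. Module 11 covers petroleum jelly tampons for a woman who has decided against dilators.

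**The concern.** The abbreviation i.e. makes dilator-related the definition of study-related, not an example of it. The arms differ in the nurse-led programme. That programme includes dilator coaching but also much else, and it is offered to women who have no dilators at all. A rule tied to one device, supplied in both arms, does not match what the programme asks women to do.

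The trial's account of harms is at stake. The Discussion anticipates national roll-out as soon as the trial ends and possible extension to other pelvic cancers. An adverse-event table built on this rule could not support a statement about the safety of the non-dilator content, or about EBRT-only women. A zero there would follow from the definition and would not be a finding.

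**Working it through.** No power, alpha or event-count arithmetic applies. The check sets the recording rule against who receives what, and then against what is measured by other routes.

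**1. Modules against the rule (Table 1).**

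| Modules | Content | Inside the rule as written? |
|---|---|---|
| 8, 9, 10 | Dilator difficulties at home, supervised dilator use, ambivalence about dilators | Yes |
| 6, 7, 11 | Gradual exposure to intercourse, pelvic floor exercises, petroleum jelly tampons | No, and physical in content |
| 1, 2, 3, 4, 5 | History, pain education, dryness and vaginal health advice, alternatives to intercourse, partner's problems | No, but mainly talk, education or advice |

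The count is 3 + 3 + 5 = 11. Three modules are inside the rule and eight are outside (11 - 3 = 8). The eight overstate the physical gap, because five of them are mainly conversation or advice, although module 3 does touch on vaginal creams. The substantive gap is modules 6, 7 and 11, plus any distress that a session itself provokes.

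**2. Module 11.** It is reached when a woman chooses not to use dilators. Bleeding or pain from the tampons recommended in their place is then not dilator-related on a plain reading.

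**3. EBRT-only women.**
- The rule requires a relation to dilator use.
- Dilator sets are given to EBRT+BT women.
- EBRT-only women in the intervention arm attend the same four core sessions and can receive the non-dilator modules.

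Their set of recordable study-related adverse events is therefore empty by definition, whatever their share of the 220 women.

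**4. Other routes by which harm is seen.**
- Clinician-examined vaginal symptoms, including blood loss, pain and dyspareunia, are graded by CTCAE in every participant at T1-T5 (Data collection; Outcome measures).
- FSDS, HADS, IES, FSQ and MMQ cover sexual, psychological and treatment-related distress, fear of sexual activity and relationship dissatisfaction. Secondary outcomes are compared between arms by intention to treat (Statistical analysis).

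**5. What those routes leave open.**
- They are recorded as outcomes at fixed times and not as events with an onset and a judged relation to a component.
- The HADS and IES look back one week and the FSDS 30 days, while T4 and T5 are six months apart (12 - 6). A short-lived event between them need not appear on these scales.
- T1 holds only the FSFI and FSDS among the questionnaires, so HADS, IES, FSQ and MMQ have no baseline value.

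**The case against.** The strongest reply is that the likely harms are measured anyway. Bleeding, pain and distress are assessed in both arms and both radiotherapy strata, with no need to attribute them to a dilator. This stands. A reader might infer from the safety section that non-dilator harms go unseen, and the documents do not support that. What remains is the event record and its attribution.

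The second reply is that this is a condensed article. The full protocol may define events more widely, i.e. may be a slip for e.g., and the text does not forbid recording other events. The article also reports ethics approval and an independent data and safety monitor. All of that is possible. The point nevertheless rests on a rule the article states, not on something it leaves out, and no other part of the article softens it. If the full protocol is wider, one corrected sentence settles the matter.

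Third, a reader might infer that dilators, being common to both arms, tell us nothing about the intervention. That goes too far. Higher dilator compliance is part of the stated hypothesis and coaching on it is an aim, so dilator exposure may differ by arm and dilator-related events are informative. They are not sufficient.

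Fourth, a reader might infer that control women have no scheduled contact at which events could surface. The documents say otherwise: vaginal symptoms are examined in all participants at the T1-T5 time points, and the nurse sessions are aligned with radiation oncology follow-up visits. The intervention arm has nurse sessions in addition, which is a reason to ask both arms the same question, but it does not show biased detection.

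**Conclusion.** The point holds in a limited form. As written, the rule confines study-related adverse events to dilator-related ones. It leaves out event-level recording of harms from gradual exposure, pelvic floor exercises, petroleum jelly tampons and session-related distress, and it gives EBRT-only women a structural zero.

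The size can be stated in components: three physical modules of 11, plus distress, and one whole radiotherapy stratum. It cannot be stated in women or events, because the article gives neither the EBRT-only share nor any expected event rate.

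The conclusion assumes that i.e. is meant literally, that EBRT-only women receive no dilator set, as the Study groups section implies, and that no wider definition exists in the full protocol. It does not imply that harms are unmeasured, since the CTCAE grades and distress scales cover much of the ground as outcomes. The trial's efficacy comparison is unaffected.

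**What to change.** 1. Replace the definition. A study-related adverse event is any untoward event possibly related to any study component (dilators, tampons, pelvic floor or exposure exercises, session-related distress), in either arm and either radiotherapy stratum.
2. Ask about such events with the same question in both arms at the existing T2-T5 time points.
3. Tabulate by arm the CTCAE vaginal grades already collected, regardless of attribution. This also avoids relying on a judgement of whether bleeding or pain after radiotherapy is due to the cancer treatment, which the exclusion sentence otherwise demands.

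The cost is one amended definition and one added questionnaire or CRF item at visits that already exist. The third step needs no new data. The downside is a little extra recording and more events to classify. Recruitment was under way when the article was published, so any event data gathered under the narrower rule should be reported separately from data gathered after the change.
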